#### Secondary outcomes

##### Proposed outcomes for the definitive trial

All other individual-level, cluster-level and economic outcome measures proposed for the definitive trial will be assessed on the response, completion rates, acceptability and the adequacy of blinding for outcome assessors during data collection. Table 2 summarises outcome measures and data collection timing. See online supplemental material 5 for collection tools.

10.1136/bmjopen-2022-063885.supp5Supplementary data

**Table 2 T2:** Schedule of outcome assessments

Outcome	Outcome measures	Data collection	Timing			
			Baseline	Every 2 weeks (end of each PLA meeting)	14 weeks (end of PLA cycle)	6 months
Proposed primary individual-level outcome	Individual Child BMI z-score	RA, CRs	✓		✓	✓
Proposed secondary individual-level outcome	Children feeding behaviour*	RA, CRs	✓		✓	✓
	Parental feeding style*	RA, CRs	✓		✓	✓
	Audio/video recording of child eating behaviours and parental feeding practices	RA	✓		✓	✓
	4-day food diary†	RA, CRs	✓		✓	✓
	Network diffusion†‡	RA, CRs	✓			✓
Proposed secondary cluster-level outcome	Children’s development performance	RA, CRs		✓		✓
	Level of dental caries	RA	✓			✓
	GP healthcare utilisation	RA	✓			✓
Economic outcome	Cost tool	RA	✓			✓
	Partners time questionnaire	RA				✓
Process outcome‡	Participants feedback*	RA, CRs		✓		
	PLA cycle meeting register*	RA, CRs		✓		
	Direct observation	RA, CRs		✓		
	Sustainability assessment	RA, CRs		✓		

*The study will have to meet the Definite Go criteria in order for the study to be feasible and to be able to proceed. However, if any one of the Definite Stop criteria is met then the study stops. The ‘Go/Stop’ indicates that it is either feasible or not feasible to proceed to a definitive trial. The progression rules have been approved by the steering and data management team. Should any of the progression rules not be met, assessments and adjustments of the NEON pilot feasibility RCT will be negotiated before proceeding to a definitive trial.

†Community Facilitators will assist in administering or completing these data collection tools before sending them to RA/CRs during the intervention period.

‡For intervention groups only.

BMI, body mass index; CR, community researchers; GP, general practitioner; NEON, Nurture Early for Optimal Nutrition; PLA, Participatory Learning and Action; RA, research assistant; RCT, randomised controlled trial.

#### Primary individual-level outcome

Child BMI z-score: HVs will measure infants’ length/height, head circumference and weight. The RA will refer to the WHO 2006 growth standard,^2^ using age-adjusted and gender-adjusted length or height(m)/weight (kg)^2^ to provide a comparison on the cluster level.

#### Secondary individual-level outcomes

Children’s feeding behaviour will be measured using six of eight domains adapted from the validated Children’s Eating Behaviour Questionnaire deemed suitable for infants: food responsiveness; enjoyment of food; emotional overeating; desire to drink; satiety responsiveness; slowness in eating; emotional undereating; and food fussiness.^7 8 22^ Obesity risk could be linked with external eating, emotional overeating and food fussiness.^7^Parental feeding style will be assessed with a validated self-reported Parental Feeding Style Questionnaire with four scales: emotional feeding; instrumental feeding; encouragement to eat and control overeating.^23^Audio/video recording of child eating behaviour and parental feeding practices^24^ involves asking participants about the meal (eg, name, ingredients) and creating annotations that link to behaviour codes identified from NEON formative study.^25^ Before-and-after audio/video recordings will be thematically analysed using Elan Software^26^ to measure intervention effect.Child food intake: The 4-day food diary^7^ is a self-reported, prospective, open-ended survey that collects detailed quantitative estimates of food consumption of infants between 4 and 18 months.^6^ It assesses nutrient intake (eg, total fat, total carbohydrate, salt, sugar) by comparing with age-specific/sex-specific UK dietary reference values.^27^ Dietary data will be presented by age group (eg, 4–6 months, 7–9 months, 12–18 months).Network diffusion of study materials between participants and their communities: CRs will track the number of downloads using the eRedbook platform. Participants will also complete a questionnaire on the number of people they shared the material with, their family size, age, gender, relationship to the participant and platform used.Equality impact assessment (EIA): This trial should reflect the diversity of the target population by enabling equal access while accommodating different needs. An EIA tool will systematically assess likely effects of the intervention on people (eg, with respect to disability, gender, ethnicity, age, sexual orientation, religion/belief), mitigate adverse impacts and identify active steps to address existing disadvantage and promote equality.

#### Secondary cluster-level routine outcomes

Although this intervention acts on the individual-level, we expect a social diffusion of good infant feeding and dental hygiene awareness and practices in the medium term to long term (online supplemental material 2: logic model). While immediate cluster-level changes are not expected, we would like to pilot cluster-level routine data collection.

Development performance of children: The Ages and Stages questionnaire (ASQ-3) includes communication, gross motor, fine motor, problem-solving and personal-social domains.^5^ Three versions are available: 24 months, 27 months and 30 months. ASQ-3 data collected by HVs during mandated visits are stored in EMIS/RIO databases.GP healthcare utilisation data is available in participants’ medical record.Level of dental caries and other signs of tooth decay is available in NHS dental services records for registered patients beginning at 6 months of age and approximately every half-year following initial visit.^17 28 29^

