### Eligibility criteria

#### Participants

Inclusion

Mothers or female carers of an infant <24 months.Indian, Pakistani, Sri Lankan or Bangladeshi background.Resident in a randomised study ward in TH, NH and WF.Willing and able to provide informed consent.

Exclusion

<18 years old.Anticipating moving out of a priori defined geographical areas before or after delivery.Current or recent participation in another study within 4 weeks of trial commencement.

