#### Control (usual care)

In all wards, HV teams have regular mandatory postnatal visits for all families of newborns and infants. These visits are immediately after birth, 6–8 weeks, 12–16 weeks, 1 year and 2–2.5 years. One optional prenatal visit is conducted by HVs between 28 and 32 weeks of pregnancy. Online supplemental material 3 lists other initiatives and resources available in each study borough as part of usual care.

10.1136/bmjopen-2022-063885.supp3Supplementary data

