### Data collection and management

Outcome data will be collected at baseline, every 2 weeks during intervention (for process measures), 14 weeks immediately postintervention, and 6 months follow-up (for economic data). During the intervention period, several outcome measurements will be administered by CFs to participants or completed by CFs and sent to CRs/RA. Other outcomes and postintervention outcomes will be assessed directly by CRs/RA (table 2). Each case will be assigned an ID. Data collected digitally or in paper format will be stored in UCL S: Drive and/or UCL cabinets. We will use RedCap electronic data management system^30^; the RedCap API allows flexible and straightforward data import and export to data analysis software.

We will form a data sharing agreement with study partners for the RA to extract and link routine cluster-level data to trial participants. To guarantee confidentiality, pseudonymised participant data will be stored on encrypted, password-protected computer or UCL S:Drive accessible only to study staff and authorised personnel. Password-protected personal data will be stored separately from trial data on secure UCL computers. Only pseudonymised quotes or data from audio/video recording may be published. Personal data and audio/video recordings will be stored for 3 years poststudy and destroyed; research data will be stored for 20 years poststudy.

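### The ASQ-3 row of Table 2 cannot be delivered as written: all infants enrol below the age of the youngest stated version, and the source is one routine visit

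*Protocol article*

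**What the plan says.** All places are in the protocol article.

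- **Entry age** (Eligibility criteria, Participants): "Mothers or female carers of an infant <24 months". No lower limit is stated.
- **Instrument** (Secondary cluster-level routine outcomes): of the ASQ-3, "Three versions are available: 24 months, 27 months and 30 months".
- **Source** (same section): "ASQ-3 data collected by HVs during mandated visits are stored in EMIS/RIO databases".
- **Visit ages** (Control (usual care)): "These visits are immediately after birth, 6–8 weeks, 12–16 weeks, 1 year and 2–2.5 years".
- **Linkage** (Data collection and management): the research assistant will "extract and link routine cluster-level data to trial participants".
- **Schedule** (Table 2): the row "Children’s development performance" is ticked under the two-weekly column and at 6 months, and not at baseline or 14 weeks. The text of Data collection and management assigns the two-weekly collection to process measures.
- **Food diary** (Secondary individual-level outcomes): it estimates "food consumption of infants between 4 and 18 months", with example reporting bands that end at 18 months. Table 2 schedules it at baseline, 14 weeks and 6 months and states no age limit.

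**The concern.** The ASQ-3 versions start at the age where eligibility ends. The outcome is also read from a record made at one routine visit, so it cannot be renewed at each group meeting. The Table 2 row therefore conflicts with the entry age, the list of visits, the description of the instrument and the text on data collection.

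This matters because of what the pilot is for. The Secondary objectives include judging completeness so as to choose outcomes and procedures for the definitive trial. Under Outcome measures for the definitive trial, missingness is to be reported overall, by time point and by arm; under Analysis, results are broken down by arm, ethnic or language group and borough. Neither separates completeness by the child's age. If the schedule is followed as written, records that could not exist because of age would be mixed with records that could have been obtained and were not. The completeness figure would then partly describe the age mix of the sample rather than the collection procedure.

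**Working it through.** The plan gives no figure of its own on this point, so there is none to reproduce. The check is age-window arithmetic.

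**Inputs.** Entry age below 24 months; ASQ-3 from 24 months; visit at 24 to 30 months; diary range 4 to 18 months; follow-up at 14 weeks (98 / 30.4375 = 3.22 months) and 6 months. The article does not settle whether 6 months runs from baseline or from the end of the cycle (3.22 + 6 = 9.22 months), so both are shown.

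**Assumptions.** The age distribution is not given; the base case is uniform over 0 to 24 months. The stated version ages are taken at face value, with 24 months as the minimum.

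**ASQ-3: share that has reached 24 months at time t.** A child qualifies if age at entry is at least 24 − t, so the share is t / 24.

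| Time point | Calculation | Share |
|---|---|---|
| Baseline | 0 / 24 | 0% |
| Week 2 | 0.46 / 24 | 1.9% |
| Week 14 | 3.22 / 24 | 13.4% |
| 6 months from baseline | 6 / 24 | 25% |
| 6 months from end of cycle | 9.22 / 24 | 38% |

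Counted from baseline, the 6-month share is 0% if all enrol under 18 months and 6 / 12 = 50% if ages are uniform over 12 to 24 months. Counted from the end of the cycle, the latter mix gives 9.22 / 12 = 77%.

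**ASQ-3: share that has had the visit.** Reaching 24 months is not enough; the visit must have taken place. If it falls evenly between 24 and 30 months, a child aged a has had it with probability (a − 24) / 6, limited to 0 and 1.

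- 6 months from baseline: the average of this probability over the six eligible months of age is 1/2, so 6 × 0.5 / 24 = 12.5%.
- 6 months from end of cycle: (6 × 0.5 + 3.22) / 24 = 6.22 / 24 = 26%.

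**Food diary: share aged 4 to 18 months.**

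| Time point | Entry ages in range (months) | In range | Out of range |
|---|---|---|---|
| Baseline | 4 to 18 | 14 / 24 = 58% | 42% |
| 14 weeks | 0.78 to 14.78 | 14 / 24 = 58% | 42% |
| 6 months from baseline | 0 to 12 | 12 / 24 = 50% | 50% |
| All three | 4 to 12 | 8 / 24 = 33% | 67% |

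If 6 months runs from the end of the cycle, the in-range share at that visit is 8.78 / 24 = 37%. The 6-month share from baseline depends heavily on the age mix: 100% if ages are uniform over 0 to 12 months, 0% if uniform over 12 to 24 months.

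**The case against.** **The outcome is exploratory routine data.** The section says "While immediate cluster-level changes are not expected, we would like to pilot cluster-level routine data collection", and learning that routine records are sparse is a legitimate pilot result. None of the outcomes discussed here is in the Go/Stop table. This limits the weight of the point but does not remove it. The data are to be linked to trial participants, so the ages of enrolled children decide what can exist, and ward-level data would not explain a tick at each group meeting either.

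**The two-weekly tick may be a slip, or shifted when the table was extracted.** That is plausible, since the dental and GP rows are ticked at baseline and 6 months. But moving the tick does not resolve the conflict: at baseline no child is old enough, and at 14 weeks about 13% are.

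**Denominators belong in the analysis plan.** True, and a missing denominator rule alone would be no finding in a condensed article. Here it is part of the remedy for a schedule that conflicts with the instrument's stated ages. The article also does not say that children outside the age range would be counted as missing.

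**The diary's age range is partly handled.** The article presents dietary data by age group, and Table 2 does not say that every child completes a diary. Use within the stated ages is a fair reading, which is why the diary is the lesser point.

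**Stronger readings that the documents do not support.** A reader might infer that age makes most planned assessments impossible. It does not: under uniform ages the diary is in range for half or more of the children at each visit counted from baseline, and BMI z-score, feeding behaviour, feeding style, recordings and GP use carry no such stated age limit. A reader might also fault the baseline dental entry because dental records begin at 6 months of age. That is a look-up for registered patients, and a younger child without a record is not a failed assessment.

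**Conclusion.** The point holds for the ASQ-3. The contradiction is certain from the text: no child is old enough at enrolment, a record from one routine visit cannot supply a two-weekly measure, and only children enrolled at 18 months or older reach 24 months by a 6-month visit counted from baseline.

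The size is less certain, because the age mix is unknown. Under uniform ages a quarter reach 24 months by that visit and about one in eight would have had the 2 to 2.5 year visit; counting from the end of the cycle raises these to 38% and 26%. These shares also rest on the visit falling evenly in its window. The diary loses some two-fifths to one half of children per visit under uniform ages, and one third can give all three diaries. That is a limit on its use, and the diary remains workable.

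This should be corrected, but it touches secondary outcomes only and puts neither the proposed primary outcome nor the Go/Stop criteria in doubt.

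**What to change.** Reconcile the participant eligibility criteria, the visit list under Control (usual care), Table 2, the food-diary and ASQ-3 descriptions, and Data collection and management. Specifically:

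1. Remove the two-weekly ASQ-3 tick, and take the ASQ-3 from the 2 to 2.5 year record where that visit falls within follow-up.
2. For the ASQ-3 and the food diary, use as denominator for completeness the children inside the instrument's age range at that time point.
3. Report the number of age-eligible children per arm beside each completeness figure.

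The cost is one corrected table row and one denominator rule. The downside is that fewer children contribute to each measure. The ASQ-3 may prove too sparse at 6 months to assess, since children who reach the visit after follow-up ends still cannot contribute; the protocol should say so.

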#### Economic outcomes

Cost: The RA will use a spreadsheet will capture the cost of the NEON Intervention Development and pilot feasibility RCT phases every 6 months.Partners’ time used: A questionnaire will capture time spent for the delivery of NEON-associated programmes.

### Data collection and management

Outcome data will be collected at baseline, every 2 weeks during intervention (for process measures), 14 weeks immediately postintervention, and 6 months follow-up (for economic data). During the intervention period, several outcome measurements will be administered by CFs to participants or completed by CFs and sent to CRs/RA. Other outcomes and postintervention outcomes will be assessed directly by CRs/RA (table 2). Each case will be assigned an ID. Data collected digitally or in paper format will be stored in UCL S: Drive and/or UCL cabinets. We will use RedCap electronic data management system^30^; the RedCap API allows flexible and straightforward data import and export to data analysis software.

We will form a data sharing agreement with study partners for the RA to extract and link routine cluster-level data to trial participants. To guarantee confidentiality, pseudonymised participant data will be stored on encrypted, password-protected computer or UCL S:Drive accessible only to study staff and authorised personnel. Password-protected personal data will be stored separately from trial data on secure UCL computers. Only pseudonymised quotes or data from audio/video recording may be published. Personal data and audio/video recordings will be stored for 3 years poststudy and destroyed; research data will be stored for 20 years poststudy.

### Analysis

Overall, quantitative and qualitative data will be analysed concurrently at multiple time points to identify early problems that are rectified as the trial progresses. Quantitative data such as the BMI z-score will be descriptively summarised using mean and SD for continuous variables, number with percentages for categorical variables and 95% CI with a breakdown of participants by trial arm, ethnic/language group and borough where relevant. An intention-to-treat analysis will also be considered. Results will be collectively assessed against the Go/Stop criteria. Before progression to the definitive trial, we will systematically and rigorously assess areas of improvement using a structured discussion tool: a process for decision-making after pilot and feasibility Trials.^31^ All statistical analyses will be done by an independent statistician who would be blinded.

#### Sample characteristics

Participant demographic characteristics will be descriptively summarised by trial arm. We will check for recruitment bias across different arms at baseline and compare later recruits who are prone to unblinded recruitment.

#### Feasibility and process measures

Across the three arms, we will check for any differential recruitment or retention rates and any consequent systematic differences in participant characteristics over time, as control arm participants may be less keen to participate or remain in the study. For the two intervention arms, we will conduct a mixed-methods implementation evaluation to explore the possibility of a blended approach in the definitive trial as some features of each delivery mode might be particularly salient. Qualitative data will be analysed thematically using framework analysis that include participants’ motivation for engagement, expectations, experiences, intervention acceptability, implementation barriers and suggestions for improvement. Negative ‘deviant’ cases will inform interpretation.

#### Outcome measures for the definitive trial

Feasibility of collecting outcome measures: To assess completeness, degrees of missingness at the individual item level and the entire outcome measure will be reported overall, by time point and trial arms. Other feasibility measures would be captured by analyses of process measures above.Intervention effect for proposed primary outcome (BMI z-score): Conditioned on low recruitment bias and sufficient adherence to trial protocol, we will estimate the difference in BMI z-score between each intervention arm vs the control arm. We will consider methods to pool data across age groups depending on the actual sample age breakdown.Sample size and power calculation for the definitive trial: Data from the pilot feasibility trial will enable us to determine (1) the smallest difference of clinical importance (through multiple testing of several key endpoints for the proposed primary outcome), (2) the clinically justifiable power-significance level or scientifically acceptable probability of ‘false positive’ (type I error) results and (3i) whether we need to adjust the calculated sample size for expected level of non-compliance/drop-in and drop-outs. We will report the ICC.Economic Evaluation: This will be conducted from a provider and user perspective which includes direct cost (eg, time, resources spent on training and participation of CF, participants’ overall household consumption and childcare costs). We will estimate the total cost, average annual cost, cost-effectiveness, equity impact analysis and compare across three arms.

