### Sample size

With communication and cultural sensitivity as key drivers of the NEON intervention, the sample size will partly depend on the coverage of ethnic and language groupings. The choice of ethnic/language groups were informed by the 2011 ONS Census^16^ and input from CFs stressing that, while language is important for communication, people’s practices are embedded in different ethnicities.

The main ethnic/language group(s) identified are: one group in TH (Bangladeshi/Bengali and Sylleti); four groups in NH (Indian/Gujrati, Indian/Punjabi, Pakistani/Urdu and Sri Lankan/Tamil); three groups in WF (Indian/Punjabi, Pakistani/Urdu, Sri Lankan/Tamil). In each borough, one women’s group PLA cycle will run per ethnic/language group per ward.

We aim to run 20–32 women’s group PLA cycle (with equal numbers of face-to-face and online PLA groups) at 6–8 participants per PLA group. Including control groups totals to 288–384 participants. Assuming an 80% recruitment or retention rate, this enables us to be 85% confident that the true population rate will fall between 0.76% and 0.84% (precision=0.04). This was estimated using a geometric mean cluster size=16 participants, cluster size coefficient of variation =0.7 and intracluster correlation coefficient (ICC)=0.02.

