#### Staff

We will recruit CFs from our local stakeholders’ network. Recruitment via CFs is particularly useful for studies with underserved or traditionally hard-to-reach populations.^21^ CFs are leaders/champions in their local community who, with training and support, help improve the health and well-being of their communities. In line with NIHR’s ‘INVOLVE’ guideline, CFs will be paid £30 for each PLA meeting and additional £5 to cover travel costs for face-to-face meetings. A comprehensive manual for the CFs will be developed with PLA experts. A tool kit will be provided to support the learnings. The CFs will attend a 3-day comprehensive workshop and additional sessions will be conducted in between the eight-meeting cycle as a refresher and address any challenges. Biweekly meetings with the RA will be conducted to discuss learnings from the sessions. The CFs will be paid through vouchers for their time similar to a 0-hour contract. HV, GP and midwives would be identified and recruited by our study partners at each study ward. Payments will be supported by NHS support costs and decided with the relevant clinical lead.

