### Intervention

#### NEON women’s group PLA cycle

The co-adapted NEON women’s group PLA cycle tailored to ethnic/language groups will be delivered face-to-face at community/children’s centre or online over 14 weeks (1 session per 2 weeks). HVs, GP and midwives’ teams will be invited to 1–2 sessions to provide evidence-based information on participants’ request. To reduce study contamination, participants may not switch wards (ie, switch arms) after treatment allocation is revealed. Figure 3 illustrates the aim of each PLA session.

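### Economic evaluation: all household spending is listed as a direct cost, which inflates every arm's cost and adds variance that can hide the cost difference between arms

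*Protocol article*

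**What the plan says.** The Economic Evaluation item, under Outcome measures for the definitive trial in the Protocol article, sets the perspective and the cost components: "This will be conducted from a provider and user perspective which includes direct cost". The examples given are "direct cost (eg, time, resources spent on training and participation of CF, participants’ overall household consumption and childcare costs". The next sentence states the outputs: "We will estimate the total cost, average annual cost, cost-effectiveness, equity impact analysis and compare across three arms". Nothing there limits consumption to spending caused by taking part, to change from baseline, or to a descriptive role.

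The Economic outcomes section describes the cost measure differently. A research assistant's spreadsheet will "capture the cost of the NEON Intervention Development and pilot feasibility RCT phases every 6 months", and a questionnaire records partners' time. The economic rows of Table 2 list only a cost tool and that questionnaire. Household spending appears in neither place.

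The one unit price in the article is in the Staff part of Recruitment: "CFs will be paid £30 for each PLA meeting and additional £5 to cover travel costs for face-to-face meetings".

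**The concern.** A user perspective is a legitimate choice, but the user costs of an intervention are those that taking part brings about: travel, childcare, time and any change in what the family buys. Rent, fuel and the general food bill are paid in all three arms and would be paid if no group ever met.

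If they are counted as direct cost, two things follow. First, the level of cost is wrong in each arm: usual care is assigned a cost equal to whatever control families spend, and any average cost or cost-effectiveness ratio built on levels is inflated. Second, the difference between arms has to be read through the variation in household spending, which depends on income and family size and carries no information about what the groups cost. Costs are among the things the abstract says the pilot will assess, so an imprecise cost comparison loses part of what the pilot is meant to deliver.

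**Working it through.** **Plan's own figure.** The article states no cost per mother, cost SD or economic sample size, so there is no economic figure to reproduce. Its one precision statement (Sample size: 85% confidence, rate 80%, precision 0.04) serves as a check on the clustering inputs.

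- Design effect, with mean cluster size 16, cluster-size CV 0.7 and ICC 0.02: DE = 1 + ((1 + 0.7²) × 16 − 1) × 0.02 = 1 + 22.84 × 0.02 = 1.457.
- 85% half-width = 1.44 × √(0.8 × 0.2 × 1.457 / N) = 0.041 at N = 288 and 0.036 at N = 384. This agrees with the stated 0.04 at the lower N, so the inputs are being read as intended.

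**Priced programme cost per mother.** The inputs are £30 per meeting online and £35 face-to-face, eight meetings ("additional sessions will be conducted in between the eight-meeting cycle", Staff) and group size "at 6–8 participants per PLA group" (Sample size).

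- Online: 8 × £30 / 8 = £30 to 8 × £30 / 6 = £40.
- Face-to-face: 8 × £35 / 8 = £35 to 8 × £35 / 6 = £46.67.
- The delivery schedule, "over 14 weeks (1 session per 2 weeks", can also be read as seven meetings. That gives £26–41 over both modes and changes nothing material.

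**Precision of an arm difference.** An equal split of 288–384 participants gives n = 96–128 per arm. The half-width is 1.96 × SD × √(2 × DE / n).

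- n = 96: 1.96 × √(2 × 1.457 / 96) = 0.3415 per £1 of SD.
- n = 128: 1.96 × √(2 × 1.457 / 128) = 0.2957 per £1 of SD.

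**Break-even SD.** This is the between-household SD of six-month spending at which noise from household spending alone gives a half-width equal to the cost in question. It needs no assumed level of spending.

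| Cost per mother | SD, n = 96 | SD, n = 128 | SD per week (÷ 26) |
|---|---|---|---|
| £30 (pay, low) | £88 | £101 | £3.4–3.9 |
| £47 (pay, high) | £138 | £159 | £5.3–6.1 |
| £300 (assumed) | £879 | £1,015 | £34–39 |
| £500 (assumed) | £1,464 | £1,691 | £56–65 |
| £1,000 (assumed) | £2,929 | £3,382 | £113–130 |

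The range of £88–159 is the widest envelope. Pairing groups of six with n = 96 and groups of eight with n = 128 narrows it to about £101–137 (£30 / 0.2957 to £46.67 / 0.3415).

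**Illustration with assumed spending.** The documents give no household spending. Assume £200–600 per household per week with a CV of 0.2–0.6. Six-month means are then £5,200–15,600 and SDs £1,040–9,360. The half-width is:

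- £355–3,196 at n = 96 with the design effect;
- £255–2,293 at n = 128 with no clustering;
- £220–1,977 at n = 128 with the design effect and baseline adjustment at an assumed correlation of 0.7.

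All of these exceed the £30–47 of facilitator pay. At the low end they do not exceed a programme cost of several hundred pounds.

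**The case against.** The strongest reply is that this is one phrase in a list of examples, in a condensed article. The article does not spell out that consumption is summed into a cost per participant. The described tools collect programme cost and partners' time, the collection instruments are in a supplement, and the valuation of user costs normally sits in a fuller document. A feeding intervention may also change food spending, which a user perspective may properly measure, and an equity analysis may need a measure of household resources.

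Part of this stands. Missing valuation detail is no fault in an article, and there are good uses for spending data. But the text does more than stay silent: it names overall consumption as a direct cost and moves straight to an arm comparison of total cost. The tools that omit it show an internal disagreement; they do not supply a limit.

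A reader might also infer several stronger things that the article does not support:

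- **That the programme costs only tens of pounds per mother.** The £30–47 is session pay. The facilitator workshop and refreshers, manual and toolkit, health-professional input, venues and childcare are named but not priced.
- **That the arm comparison is mostly noise.** Against facilitator pay it is, over every spending range tried. Against full cost it depends on figures that are not given.
- **That arm differences would be biased by which wards fell where.** Wards are randomised, stratified by borough (Randomisation), so ordinary spending cancels in expectation. Chance imbalance remains, with four to six wards per arm (the abstract says 12 wards, Design says 18).
- **That these figures decide the delivery mode.** Table 1 has no cost criterion, and Feasibility and process measures gives that question to the mixed-methods evaluation.
- **That development and research costs are pooled with delivery cost.** The spreadsheet covers both phases, but no pooling rule is stated.

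**Conclusion.** The point holds as a wrongly specified cost component in a secondary analysis of a pilot. Followed as written, the plan inflates the cost of every arm and widens the interval for the cost difference, without biasing its expectation.

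A between-household SD of only about £3–6 per week in spending is enough for the half-width to match all the programme cost that the article prices. If full cost is £300–1,000 per mother, the matching SD is about £34–130 per week, and whether noise dominates cannot be settled from the article.

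The sizes rest on three assumptions: an equal split across arms, the recruitment and retention ICC and cluster-size CV carrying over to cost, and, for the illustration only, the assumed spending levels and CVs. The disagreement between the Economic Evaluation item and both the Economic outcomes section and Table 2 rests on none of them.

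**What to change.** In the Economic Evaluation item, replace the overall household consumption example with out-of-pocket and time costs attributable to participation or to changed feeding or dental practice, such as travel, childcare and change in infant food spending. If overall consumption is collected, state that it serves only as a socioeconomic descriptor for the equity analysis and does not enter total cost or cost-effectiveness. Then align the Economic outcomes section and the economic rows of Table 2, so that each user cost named in the analysis has a stated tool and time point.

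The cost is a wording change and slightly more specific cost questions for participants. Reported costs per arm will be smaller.
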